## Abstract

**Background:**

Family caregivers of patients with severe illness and in need for a palliative care approach, face numerous challenges and report having insufficient preparedness for the caregiver role as well as a need for information and psychosocial support. Preparing to care for a severely ill family members also means becoming aware of death. Feelings of being prepared are associated with positive aspects and regarded protective against negative health consequences.

**Methods:**

The study adheres to the SPIRIT-guidelines (Supplementary 1), uses a pre-post design and include a web-based intervention. Inclusion criteria are; being a family caregiver of a patient with severe illness and in need of a palliative care approach. The intervention which aims to increase preparedness for caregiving and death is grounded in theory, research and clinical experience. The topics cover: medical issues, symptoms and symptom relief; communication within the couple, how to spend the time before death, being a caregiver, planning for the moment of death and; considerations of the future. The intervention is presented through videos and informative texts. The website also holds an online peer-support discussion forum. Study aims are to: evaluate feasibility in terms of framework, content, usage and partners’ experiences; explore how the use of the website, influences family caregivers’ preparedness for caregiving and death; explore how the use of the website influences family caregivers’ knowledge about medical issues, their communication with the patient and their considerations of the future; and to investigate how the family caregivers’ preparedness for caregiving and death influences their physical and psychological health and quality of life 1 year after the patient’s death. Data will be collected through qualitative interviews and a study-specific questionnaire at four time-points.

**Discussion:**

This project will provide information about whether support via a website has the potential to increase preparedness for caregiving and death and thereby decrease negative health consequences for family caregivers of patients affected by severe illness. It will provide new knowledge about intervention development, delivery, and evaluation in a palliative care context. Identification of factors before death and their association with family caregivers’ preparedness and long-term health may change future clinical work.

**Trial registration:**

The study is registered at ClinicalTrials.gov: NCT03676283.

## Background

Although there are great variations, family caregivers of patients with severe illness often face numerous tasks involving the practical and medical caregiving for the patient while also providing emotional, social and existential support as well as maintaining household chores [1]. They may or may not recognize themselves as caregivers; nevertheless, the scientific literature defines a family caregiver as any relative, friend, or family caregiver who has a significant relationship with, and provides various forms of assistance to, an ill person. Thus, the term ‘caregiving’ covers a broad perspective [2]. Family caregivers often report being insufficiently prepared for the caregiver role as well as a consequent need for information and psychosocial support [3, 4]. Preparedness for caregiving refers to how ready the family caregivers themselves perceive they are for the tasks related to the caregiving role, such as providing physical care, emotional support and dealing with the stress of caregiving. Thus, preparedness for caregiving has both a practical and emotional component; knowing what to do, but also coping with emotions and stress [5]. Feelings of being prepared are associated with several positive aspects, such as less burden and anxiety, and can be regarded as a protective factor against negative consequences. Preparedness may also promote stronger feelings of reward and hope as well as better health [6, 7]. Increased feelings of preparedness for family caregivers have been suggested to possibly affect the patient in a favorable way [8].

In palliative care, family caregivers also need to prepare for the patient’s death [3]. Preparedness for death refers to being aware that an impending death may occur at any moment. Through interviews, it has been found that preparing to care for a severely ill family member also means becoming aware of death [9–11]. Awareness of death can be frightening and can result in a very tense situation [11], however, it can also be helpful; contributing to a sense of having control over the situation [9]. Results from a nation-wide study of widowers showed that a high level of preparedness promoted their long-term well-being [12]. In one study of a bereaved population, 25% reported that health-care professionals could have done more to prepare the bereaved for the death of their loved one. The bereaved believed that the physicians’ lack of communication concerning the prognosis and impending death hindered them from being able to prepare [13]. Results from other studies have indicated that end-of-life discussions, preparedness for death, encouragement of advanced care planning and reducing family caregivers’ distress before the loss, may also improve adjustment after the loss [14, 15]. Most people seem to adjust to the caregiver role [16, 17] and to the loss of a close person and recover from the emotional strain. However, some suffer beyond what can be viewed as normal grief, i.e., they experience a long-lasting decline in their mental and physical health [18–21] and are even at an increased risk of death [20, 22]. Interventions with various designs have had significant positive effects on family caregivers’ feelings of preparedness for caregiving [23–25]. Intervening before the death of the patient, providing more information and support, and thereby increasing preparedness, may also lessen the burden of bereavement.

Most interventions were earlier delivered either face-to-face or in written documents. Now the internet is a natural platform for distributing information, with its unique advantage of easy accessibility and the potential to diminishing geographic and time barriers. The use of web-based interventions to support family caregivers has increased lately. A total of 12 systematic literature reviews [26–37] report on various web-based interventions, half of them focusing on family caregivers of patients diagnosed with dementia, and the others focusing on caregivers of patients affected by cancer or chronic conditions. The reviews all conclude that content, structure and duration differ markedly between the reported interventions, which included various designs; online support groups, informational websites, websites combined with telephone support or email support, and websites combined with exchange with other caregivers online. Altogether, the reviews report a range of improved family caregiver outcomes, such as increased knowledge, self-efficacy, self-esteem, coping skills, wellbeing and reduced anxiety, depression, stress, strain, and burden [26]. Overall, the reviews conclude that web-based family caregiver interventions can be beneficial in offering information and support, but more research is needed.

The strained situation for family caregivers of patients affected by severe illness and in need of a palliative care approach is by now known, and the positive influence of feeling prepared has now been proven [26]. Several web-based interventions to support family caregivers have been developed and are reported to have positive outcomes and improvements for family caregivers. However, there is still a need to examine whether a web-based intervention can be used in the context of palliative care to promote family caregivers’ preparedness for caregiving and death. Thus, the aim of this paper is to describe a study protocol which addresses this subject.

## Methods

### Design

The study adheres to the SPIRIT guidelines (Supplementary 1) and uses a pre-post design to evaluate an intervention that is delivered and presented on the website narstaende.se. The intervention is a complex intervention, as defined by the Medical Research Council guidance [38, 39], because it comprises a number of interacting components, a number of behaviors required by those receiving the intervention, and a number of outcomes and flexibility in the use of the intervention. The study follows the steps that are significant in considering a complex intervention, which are: development based on existing evidence and theory, assessing feasibility, assessing effectiveness, understanding processes, and measuring outcomes. The study is registered at ClinicalTrials.gov NCT03676283.

### The intervention

#### Intervention content and design

The overall aim of the intervention is to increase preparedness for caregiving and death in family caregivers of patients affected by severe illness and to decrease the risks of negative health consequences. The intervention content rests on evidence and previous research, as well as clinical experience, and addresses topics shown to be associated with preparedness. The topics cover: a) medical issues, including symptoms and symptom relief; b) communication within the couple, how to spend the time before death, being a family caregiver or caregiver, planning for the moment of death; and c) considerations of the family caregiver’s future, including psychological issues, logistical issues, finances, and the care of children (Table 1). The intervention is presented in the Swedish language at the website närståede.se through videos and informative texts. The videos show conversations, addressing intervention topics between family caregivers (played by actors) and different health-care professionals (authentic). The informative texts complement, deepen and broaden the topics raised in the videos. As a part of the intervention, there is also an online peer-support discussion forum at the website, which can be used by family caregivers to communicate with others in a similar situation. The website narstaende.se, solely hosts the intervention and is co-designed between health-care researchers, clinical health-care professionals, information systems researchers, a digital communication strategist and IT-consultants. The website will be accessible from mobile phones, tablets and computers. All interaction with the site, and the related information and user credentials, is encrypted and secured according to the GDPR directive (EU 2016/679).

**Table 1 Tab1:** Topics addressed in films and texts

To think through whether she or he spends as much time with the patient as she or he wants.	
To think through the dual role that might evolve as being a family member and a caregiver. To think through whether she or he participates in the patient’s care according to her or his own wishes.	
To communicate with the patient about the disease’s physical aspects in a structured way. To have knowledge of common symptoms that may occur, such as pain, constipation and others, and how to deal with them.	
To communicate with the patient about funeral-related issues.	
To communicate with the patient about financial questions and writing a will.	
To communicate, if applicable, with the patient about their children’s well-being and future.	
To communicate with the patient about her or his psychological symptoms and feelings relating to the impending death.	
To communicate, if appropriate, with the patient about emotional issues from the past, such as unfinished business, coming to closure, forgiveness and giving thanks.	
To imagine herself or himself as bereaved 6 months after the patient’s death, and considering the psychological and practical implications.	
To imagine, cognitively and emotionally, the patient’s death.	

#### Theoretical framework

In addition to the body of empirical research about preparedness for caregiving and death, Andershed and Ternestedt’s theoretical framework [40] was used in guiding the development and design of the intervention. The framework derives from qualitative data and focuses on the involvement and principal needs of family caregivers in palliative care and is used here to enhance the understanding of the caregiver situation. The framework is clearly written on an abstract level but is relatively easy to absorb and could therefore serve as a guide for practice. The framework illustrates three components of principal needs; these are knowing, being and doing. These components are closely related to the concept of preparedness. Knowing represents family caregivers’ need for, and active seeking of, knowledge, which is a prerequisite for being and doing. Family caregivers try to increase their understanding of the patient’s condition by actively seeking knowledge of, for example, the patient’s symptoms, diagnosis, and prognosis. Being concerns emotional aspects, such as spending time with the patient and sharing his or her world. Doing has a more practical aspect and involves the family caregiver doing things for the patient, such as helping the patient with hygiene or medication, or keeping in contact with friends and family [41]. The theoretical framework further strengthens the content and the choice of topics in the intervention, which is tailored to meet the family caregivers’ need for knowing, being and doing.

### Aims

The overall aim of the research is to examine the use of and potential influences of a web-based intervention targeting family caregivers of patients affected by severe illness who are cared for at home. To reach a deeper understanding for such an approach, the following four specific aims will be addressed:
Specific aim I: To evaluate feasibility in terms of framework, content, usage and family caregivers’ experiences of a web-based psycho-educational intervention. *Family caregivers will be interviewed and statistics concerning their use of the website will be used.*Specific aim II: To explore how the use of a website influences family caregivers’ degree of preparedness for caregiving and death. *Preparedness for caregiving will be measured at baseline and 4 weeks later. Preparedness for death and associations with preparedness for caregiving will be measured 8 weeks after the patient’s death. Interviews will also be used for data collection.*Specific aim III: To explore how the use of a website influences family caregivers’ knowledge about medical issues, their communication with the patient, and their considerations of the future. *Measurements will be performed at baseline and 4 weeks later. Interviews will also be used for data collection.*Specific aim IV: To investigate how family caregivers’ degree of preparedness for caregiving and death influences their physical and psychological health and quality of life 1 year after the patient’s death. *Information collected as described for the specific aims II and III will be related to physical and psychological health, measured 1 year after the patient’s death.*

### Inclusion criteria for patients and family caregivers

This study focuses on family caregivers of patients affected by severe illness who are enrolled in specialized home care. The inclusion criteria are; being a family caregiver, over 18 years old, of a patient affected by severe illness and in need of a palliative care approach (“It is probably a matter of months, not years”). Severe illness is here understood as any acute or chronic illness and/or condition that causes significant impairment, and may lead to long-term impairment, disability and/or death [42]. Equally important is that the patient must have a cognitive function sufficient for communication. The patient should have been informed that his or her illness cannot be cured. Family caregivers need to understand and speak Swedish. To obtain enough data after attrition, we plan to recruit 200 family caregivers.

### Recruitment

Altogether, directors of departments covering 30 specialist palliative home care units have given written informed consent for recruitment of family caregivers. The home care units are staffed with multi-disciplinary teams of health-care professionals, including nurses, physicians, physiotherapists, occupational therapists, dieticians and social workers delivering 24-h care in private homes. Health-care professionals employed in the settings will recruit family caregivers, according to the inclusion criteria, until the recruitment target has been reached, which is expected to be within a period of approximately 1 year and a half. Initially, the patient will be approached by a health-care professional who will provide them with written information about the study. The health-care professional will also ask the patient whether the researchers have their permission to contact his or her family caregiver/s for information about the study. The patient can thus nominate one or more family caregivers to the study. If a family caregiver is present at the time of recruitment, he or she will receive the information by the same time as the patient. If the patient agrees that his or her family caregiver/s can be contacted, two different scenarios can take place: 1) the health-care professional is given a telephone number for the family caregiver/s and registers the number in an administrative database, whereupon a research assistant calls the family caregiver/s to provide study information and a request to participate; or 2) the patient informs the family caregiver/s or the family caregiver/s has been present at the time for recruitment and pays a visit to the website on his or her own initiative. After agreeing to consider participation, the family caregiver/s registers at narstaende.se, where they have access to text informing them about the study and where they can give their consent to participate. If they agree to participate, the family caregivers will be asked to complete a baseline questionnaire electronically (Fig. 1).

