#### Statistical analysis

In the analysis of preparedness for caregiving (aim II), we will address the statistical null hypothesis by analyzing mean differences between two dependent means (pre- and post-intervention). Cut-off values for low, moderate and high preparedness have been established through earlier studies [24] and will be applied to the results. Preparedness for death (aim II) will be examined using descriptive statistics, and associations with preparedness for caregiving will be investigated with the use of linear regression analysis. Guided by the intention-to-intervene (intervention to treat) principle, we will include all family caregivers for whom we have information on the respective outcome. For aims III and IV we will proceed in a similar manner.

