#### Statistical power

Statistical power was calculated based on the preparedness for caregiving scale [5, 46]. As a model, we used a previous intervention study [24], where a statistically significant (alpha = 0.05) improvement in preparedness for caregiving was observed between two dependent means (*t*-tests) with an effect size of 0.27. In order to obtain statistical power of 80%, we would need 109 participants. However, with regard to the number of attritions in the previous intervention study, we decided to raise the required sample to 200 participants.

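### Several caregivers may share one patient, but the pre-post test, the regressions and the 109 needed for 80% power treat every caregiver as independent

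*Protocol article*

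**What the plan says.** Three parts of the protocol article bear on this.

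- **Recruitment.** "The patient can thus nominate one or more family caregivers to the study". No maximum or expected number per patient is given. The same section reports that "directors of departments covering 30 specialist palliative home care units have given written informed consent for recruitment of family caregivers".
- **Statistical analysis.** Preparedness for caregiving (aim II) will be tested by "analyzing mean differences between two dependent means (pre- and post-intervention". Preparedness for death will be described, and "associations with preparedness for caregiving will be investigated with the use of linear regression analysis". Aims III and IV are to be handled in a similar way. No patient-level term, robust standard error or other allowance for clustering is mentioned.
- **Statistical power.** The model is an earlier intervention study in which "a statistically significant (alpha = 0.05) improvement in preparedness for caregiving was observed" in a dependent-means comparison "with an effect size of 0.27". The result is: "In order to obtain statistical power of 80%, we would need 109 participants". The section then says that, "with regard to the number of attritions in the previous intervention study, we decided to raise the required sample to 200 participants". Attrition is the only reason given for going from 109 to 200, and no rate is stated.

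**The concern.** The word dependent in the analysis section covers two measurements of one caregiver. It does not cover two caregivers of one patient. Co-nominated caregivers share the patient, the illness course and the home-care team, and for the outcomes at 8 weeks and 1 year they share one death. Several aim III outcomes concern communication with that same patient. It is therefore plausible that their changes in preparedness are positively correlated.

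A test that ignores such correlation uses too small a standard error. It then rejects a true null hypothesis more often than the stated 5%, and a sample size derived from it promises more power than it delivers. The recruitment rule thus conflicts with an assumption on which both the named test and the printed sample size rest.

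**Working it through.** **Inputs from the protocol:** effect size 0.27, alpha 0.05, power 80%, 109 participants, target 200, 30 units.

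**Inputs assumed because the documents do not give them:** m, the number of study caregivers per patient, 1.2 to 2; and the ICC of change scores within a patient, 0.1 to 0.5.

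**1. Reproduce the 109.** For a two-sided paired test with independent participants, n = (1.960 + 0.842)² / 0.27² = 107.7, so 108. The exact noncentral-t calculation gives 110, and power at 109 is 79.8%. The stated 109 agrees with this. A one-sided test gives 85 (normal) or 87 (t) and does not. No design effect is needed to reach 109, so none is included.

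**2. Add clustering by patient.** Design effect DE = 1 + (m − 1) × ICC. The other columns follow from it:

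- required number = 109 × DE, rounded up;
- power at 109 = noncentral-t power at an effective n of 109/DE;
- true alpha ≈ 2 × P(Z > 1.96/√DE);
- tolerated attrition = 1 − required number/200.

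| m | ICC | DE | Required for 80% | Power at 109 | True alpha | Attrition tolerated from 200 | Power if all 200 analysed |
|---|---|---|---|---|---|---|---|
| 1.2 | 0.1 | 1.02 | 112 | 79.0% | 5.2% | 44% | 96.4% |
| 1.3 | 0.3 | 1.09 | 119 | 76.2% | 6.0% | 40.5% | 95.3% |
| 1.5 | 0.3 | 1.15 | 126 | 73.9% | 6.8% | 37% | 94.3% |
| 2.0 | 0.3 | 1.30 | 142 | 68.6% | 8.6% | 29% | 91.4% |
| 2.0 | 0.5 | 1.50 | 164 | 62.2% | about 11% | 18% | 87.2% |

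Under independence the tolerated attrition is 1 − 109/200 = 45.5%. The naive standard error is too small by a factor of √1.02 = 1.01 to √1.50 = 1.22.

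Starting from the exact 110 instead of 109, a DE of 1.15 requires 110 × 1.15 = 126.5, so 127, and tolerates 1 − 127/200 = 36.5% attrition.

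**3. Unequal numbers per patient.** If a share f of caregivers come in same-patient pairs and the rest are single, DE = 1 + f × ICC. With f = 0.5 and ICC 0.3 this is again 1.15, and a simulation of the paired t-test at n = 110 gave a type I error of 6.8%. So m in the table is best read as the average seen from the caregiver's side. If m is a plain average over patients, a mix of singles and pairs gives a somewhat larger DE. For example, a plain mean of 1.5 puts 1.0/1.5 = 2/3 of caregivers in pairs, and DE = 1 + 0.667 × 0.3 = 1.20.

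**4. Regressions.** For a slope, the inflation is about 1 + (m − 1) × ICC of the covariate × ICC of the residual. With m = 2 and both ICCs at 0.3 this is 1.09, against 1.30 for the mean change.

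**5. Units.** 109/30 = 3.6 caregivers per unit. An assumed unit ICC of 0.01 to 0.05 gives DE 1.03 to 1.13 and power at 109 of 78.7% to 74.6%.

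**The case against.** The strongest reply is that the plan recruits 200, not 109. Every required number in the table is below 200, and if all 200 were analysed, power would be 87% to 96%. This stands as far as it goes. A reader might infer that the trial is underpowered, but the documents do not show that: a shortfall depends on an attrition rate they do not state. The reply does not settle the matter, because a larger sample does not correct the type I error of the named test, and the margin above 109 is already assigned to attrition.

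Second, permission to nominate several caregivers is not an expected number. If few patients do so, the effect is negligible, as the first row of the table shows. The relevant ICC is also that of change, and differencing removes the stable part of what caregivers share. Both points stand, so no single figure can be defended.

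Third, a reader might conclude that all standard errors for aims II to IV are too small to the same degree, or that clustering is stronger after the death. The first fails because slopes are inflated less than a mean change and part of aim II is descriptive. For the second, the documents give no figure.

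Fourth, a unit-level adjustment might seem equally necessary. The support is weak: this is a single-group study of one website, telephone help comes from the researchers, and units serve mainly to recruit.

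Finally, an unseen analysis plan may specify clustered errors, and follow-up timed to the patient's death suggests that some link between caregiver and patient exists. Both are possible. Neither changes the printed power figure, which was derived under independence.

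**Conclusion.** The point holds in conditional form. The recruitment rule allows caregivers to share a patient, and the named analyses and the 109 make no allowance for it. With any positive within-patient correlation of change, the paired-test standard error is too small, alpha exceeds 0.05, and 109 analysed caregivers give less than 80% power. How far depends on two undocumented inputs: over the assumed ranges the consequence runs from trivial to substantial. It is not established that the trial will miss 80% power with 200 recruited. The printed calculation simply does not support that figure under this recruitment rule. This is a correction to the analysis and the power statement and gives no reason to change the design or the recruitment target.

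**What to change.** 1. Keep a patient identifier that links co-nominated caregivers. Confirm that it also covers caregivers who register on the website themselves and that it survives coding of names. If the link is not captured, the analysis cannot be corrected later.
2. Use patient-cluster-robust standard errors for the aim II pre-post test and for the aim II to IV regressions. A patient random effect on the change score is an acceptable alternative for the pre-post test. A fuller multilevel model is unnecessary, and a unit term is optional.
3. Restate the power paragraph with an assumed number of caregivers per patient, an ICC and the resulting design effect, applied before attrition. With a design effect of 1.15, for example, about 127 analysed caregivers are needed. Keep the target of 200 and state the attrition it then tolerates, about 36%.

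The cost is some analysis wording, one linking variable if it is not already held, slightly wider intervals and a less favourable stated power. No extra participants are needed.
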